#### Analysis of Secondary Outcomes

GLM was used to obtain differences in effect sizes and their 95% CI for continuous variables between groups. Categorical variables were described in absolute numbers (percentages) and GLM was used to obtain differences in effect values and their 95% CI, using logistic for family function and logit for link function.

Statistical analyses were conducted using Stata 16.0 software (StataCrop). All statistical tests were 2-sided with a significance level of α=.05. Differences were considered statistically significant at *P*<.05.

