### Participants Eligibility Criteria

Eligible participants must meet the following criteria: (1) be aged between 6 and 18 years, (2) be overweight [23], and (3) have gastric-heat and dampness-obstruction syndrome [16].

Overweight or obesity with gastric-heat and dampness-obstruction syndrome was defined as follows:

(1) The “Expert Consensus on Diagnosis, Assessment, and Management of Obesity in Chinese Children” states that BMIs between 85% and 95% were classified as overweight, while those above 95% were classified as obese for children of the same gender and age [23].

(2) The “Pediatrics of Traditional Chinese Medicine” framework [16] outlined the conditions that must be met for the gastric-heat and dampness-obstruction syndrome, which include (1) dizziness and heaviness in the head, (2) thirst, (3) rapid digestion of food and polyorexia, (4) heaviness of limbs, (5) fatigue body and lack of strength, (6) a red tongue, (7) greasy fur, and (8) a slippery pulse. It is important to note that conditions (7) and (8) must be satisfied, while conditions (1) to (6) must be satisfied at least 3 conditions.

Participants who met any of the following exclusion criteria were excluded: (1) having hereditary obesity or obesity caused by endocrine disorders, such as Cushing syndrome, primary hypothyroidism, and hypothalamic obesity; (2) currently being enrolled in other clinical trials or having participated in another clinical trial in the past 3 months; (3) self-administration of oral weight-loss medications or other forms of meal replacements; and (4) having serious organic diseases of the heart, liver, kidneys, or brain, or infectious diseases or psychiatric disorders.

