#### Secondary Outcomes

Secondary outcomes included body weight, waist circumference, waist-to-height ratio, BMI, blood pressure (BP), body fat content, glucose metabolism, blood lipid levels, liver and kidney function, composition of gut microbiota, and TCM syndrome score, and were assessed at the end of 1 month and 3 months, respectively.

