**Assessments**														
	General investigation			N/A		✔		✔		✔		N/A		
	Anthropometry (Height, Weight, WC^b^, and BP^c^)			N/A		✔		✔		✔		N/A		
	Body fat content			N/A		✔		✔		✔		N/A		
	Indexes of liver and renal functions			N/A		✔		✔		✔		N/A		
	Indexes of glucose metabolism			N/A		✔		✔		✔		N/A		
	Levels of serum lipid			N/A		✔		✔		✔		N/A		
	TCM^d^ syndrome score			N/A		✔		✔		✔		N/A		
	Gut microbiota			N/A		✔		✔		N/A		N/A		
	Dietary data			N/A		✔		✔		✔		N/A		
	Exercise data			N/A		✔		✔		✔		N/A		
	Adverse events			N/A		N/A		✔		✔		N/A		

^a^N/A: not applicable.

^b^WC: waist circumference.

^c^BP: blood pressure.

^d^TCM: Traditional Chinese Medicine.

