#### Analysis of Primary Outcome

The primary outcome in this study was the change in body weight from baseline to 1 month. A generalized linear model (GLM) was used to compare the difference in weight change between the groups, with the baseline body weight as the covariate, to obtain the estimate of the mean difference in body weight change and its 95% CI, using Gaussian for family function and identity for link function.

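### The continuous secondary outcomes are listed as follow-up measures and their model names no baseline covariate, so an analysis run literally would be needlessly imprecise

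*Protocol article*

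**What the plan says.** The Primary Outcome section defines the primary endpoint as a change in weight over 1 month. Analysis of Primary Outcome then gives a full model: change as the response, a Gaussian family, an identity link, and adjustment "with the baseline body weight as the covariate".

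The Secondary Outcomes section is worded differently. It opens "Secondary outcomes included body weight, waist circumference, waist-to-height ratio, BMI, blood pressure (BP), body fat content, glucose metabolism, blood lipid levels", continues through organ function, gut microbiota and the TCM syndrome score, and says that these "were assessed at the end of 1 month and 3 months, respectively". The word change does not appear.

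Analysis of Secondary Outcomes says of the continuous measures that "GLM was used to obtain differences in effect sizes and their 95% CI for continuous variables between groups". No covariate, family, link or form of response is given. For categorical variables it specifies a GLM "using logistic for family function and logit for link function".

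Table 1 schedules all these measures at baseline as well as at follow-up. Eligible children must "be aged between 6 and 18 years", and Randomization and Blinding describes simple 3:1 randomisation.

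**The concern.** The article uses the language of change and baseline adjustment for the primary outcome and drops both for the secondary ones. A programmer working from this text alone would fit follow-up value on group and nothing else.

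Over an age span of 6 to 18 years, children differ in weight, waist and BMI far more than a month of either intervention is expected to change them. With no baseline term, all of that spread goes into the error variance. The stated aim is cardiometabolic risk, and apart from weight it is addressed only through these secondary outcomes.

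Body weight at 1 month is in effect both the primary and a secondary outcome. Unless the secondary model contains baseline weight, the same data can give two visibly different estimates of the same treatment effect.

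**Working it through.** **Inputs from the article (Sample Size).** Difference 0.5 kg; SD 1.1 kg, read as the SD of the 4-week change and taken from a pilot of 12 patients; power 0.80; two-sided α 0.05; 150 TAAT and 50 ILCD.

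**Assumptions not in the article.** Between-child SD of body weight, 5 to 20 kg. Correlation r between baseline and follow-up for the other outcomes, 0.3 to 0.95.

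**1. Reproduce the plan's own figure.** With 3:1 allocation, the control-arm size is (1.96 + 0.8416)² × 1.1² × (1 + 1/3) / 0.5² = 7.849 × 1.21 × 1.333 / 0.25 = 50.6. That rounds up to 51, with 153 in the TAAT arm. The plan states 50 and 150, at which power is 79.5% by the normal approximation. The planned size reproduces closely, and it rests on the SD of change.

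**2. Precision for 1-month body weight.** SE = SD × √(1/50 + 1/150) = 0.1633 × SD. The 95% half-width is 1.96 × SE. Power for 0.5 kg is Φ(0.5/SE − 1.96) + Φ(−0.5/SE − 1.96).

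| Response | SD (kg) | SE (kg) | 95% half-width (kg) | Power for 0.5 kg |
|---|---|---|---|---|
| Change, planned SD | 1.1 | 0.18 | 0.35 | 79.5% |
| Raw level, assumed SD | 5 | 0.82 | 1.6 | 9.4% |
| Raw level, assumed SD | 10 | 1.63 | 3.2 | 6.1% |
| Raw level, assumed SD | 15 | 2.45 | 4.8 | 5.5% |
| Raw level, assumed SD | 20 | 3.27 | 6.4 | 5.3% |

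The interval for raw levels is wider by a factor of SD/1.1, which is 4.5 at 5 kg and 18.2 at 20 kg. Adding baseline weight as a covariate leaves a residual SD of at most about 1.1 kg, so the first row also serves for the adjusted analysis.

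**3. Other continuous outcomes.** With the outcome's own baseline as covariate, the residual variance is (1 − r²) of the raw variance. For an unadjusted change score it is 2(1 − r), if the variance is the same at both visits.

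| r | Adjusted / raw variance | Change score / raw variance |
|---|---|---|
| 0.3 | 0.91 | 1.4 |
| 0.5 | 0.75 | 1.0 |
| 0.8 | 0.36 | 0.4 |
| 0.95 | 0.10 | 0.1 |

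Adjustment saves more than half the variance only when r exceeds √0.5 ≈ 0.71. Analysing change without the covariate is not an equivalent remedy: below r = 0.5 it is less precise than the raw level.

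**4. Agreement with the primary result.** Let Y0 and Y1 be baseline and 1-month weight and G the group. If Y1 = a + bG + cY0, subtracting Y0 gives Y1 − Y0 = a + bG + (c − 1)Y0. The group coefficient b is the same, so on the same participants the adjusted 1-month weight and the primary analysis give the same estimate.

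**The case against.** The strongest reply is that the article is silent, not wrong. No sentence says that the secondary outcomes are analysed as raw values or without baseline. The secondary section follows directly on the primary one and, for continuous variables, omits the family and link as well as the covariate. A reader who carries over the Gaussian family and identity link could as well carry over baseline adjustment. The Secondary Outcomes sentence can be read as giving visit timing only. A full protocol, version 2.0, exists and may settle the matter. All of this stands. It is why the point concerns what the text leaves open, and why it is offered as a free improvement and not as a demonstrated error.

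A reader might infer more than the documents support:

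- **That most of the precision is lost for every secondary outcome.** The document's own SD anchors this for body weight only, and even there the between-child SD is assumed. For blood pressure, laboratory values and the TCM score, the loss depends on correlations that are not given and could be modest.
- **That chance imbalance under simple randomisation biases the estimates.** It does not. Randomisation keeps the unadjusted comparison unbiased, and its wide interval already reflects chance imbalance.
- **That an unadjusted weight result would contradict the primary one.** The estimates could differ a good deal, but a wide interval around a noisy estimate is not contrary evidence.
- **That the categorical model is invalid.** Logistic is not the name of a GLM family, but the stated logit link makes the intended model clear, and Secondary Outcomes names no categorical outcome.

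An age- and sex-standardised BMI score, and age and sex in the primary model, are optional preferences and not part of this point.

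**Conclusion.** The point holds as a gap in specification with a cost in precision. The primary outcome has a stated response form and baseline covariate; the continuous secondary outcomes have neither. For body weight, the conclusion that a literal analysis would be far less precise holds over the whole assumed SD range of 5 to 20 kg, with power for 0.5 kg falling from about 79% to between 5% and 9%. It also assumes that the pilot SD of 1.1 kg is an SD of change. For the other outcomes the gain from adjustment is real but of unknown size: 9% of the variance at r = 0.3, 25% at 0.5, 64% at 0.8. The primary analysis and the sample size are not affected.

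**What to change.** In Analysis of Secondary Outcomes, state that each continuous secondary outcome is analysed at 1 month and at 3 months, where Table 1 schedules it, by a GLM with Gaussian family and identity link containing group and that outcome's own baseline value. With that term included, level and change give the same group difference, and the secondary 1-month weight agrees with the primary.

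For any categorical outcome, name the family as binomial and state the effect measure: an odds ratio from the logit link, or a risk difference from the model margins.

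The cost is a sentence or two and a few lines of code. No new data are needed. By the article's dates recruitment runs to December 2025, so the wording can be settled before the database is locked and analysed. If the full protocol or SAP already says this, the article need only be brought into line with it.

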### Ethical Considerations

This study has been approved by the Medical Ethics Committee of the Children’s Hospital of Fudan University and will be conducted in accordance with the approved guidelines and regulations of the participating institution (approval number 2021 [.350]). This trial was conducted in accordance with the current version (AP_IDR_2.0) of the protocol, which has been registered at ClinicalTrials.gov. Informed written consent was obtained from all patients before inclusion in the study. As the involvement of the patients were voluntary, the study could be stopped at any time. All records that contain names or other personal identifiers were stored separately from study records identified by code number. The identification of participants in any images of the manuscript or supplementary material was impossible. For example, the researchers provided the necessary recording materials and sample collectors. The intervention method did not entail additional costs for the participants; thus, no compensation was required.

## Results

The protocol was registered on ClinicalTrials.gov (NCT05847478) on May 5, 2023. The current protocol is version 2.0, dated February 28, 2023, which is the final version as approved by the institutional ethical committee. Recruitment started in June 2023 and is expected to be completed in December 2025. By November 2024, we had enrolled 112 participants (Figure 3).

**Figure 3 figure3:**
[figure not shown]
Flowchart of the study. TCM: traditional Chinese medicine; T0: baseline; T1: intervention for 1 month; T2: intervention for 3 months.

## Discussion

### Anticipated Findings

It is hypothesized that TAAT will prove superior to ILCD in controlling body weight through this clinical trial. In addition, it is anticipated that the mechanistic differences between the 2 nondrug intervention methods will be elucidated. This study will be the first randomized controlled trial to investigate the effect and safety of TAAT compared with ILCD for overweight or obesity and other cardiometabolic risk factors. Previous studies on the effects of auricular treatment have mainly focused on adolescents and adults [12,14]. A study was conducted as a randomized controlled trial to examine the effects of auricular acupressure on obesity improvement in children. However, this trial had a small sample size and did not take into account the impact of diet, exercise, and lifestyle on body weight [15]. Consequently, there is a lack of high-quality clinical trials on the effects of TAAT in children with obesity, although we found some clinical evidence of this approach in children. Furthermore, the participants’ gut microbiota will be studied in order to explore the underlying mechanisms of the 2 different interventions.

All participants in this study are patients from the Department of TCM and seeking TCM intervention. As one of the treatment methods in TCM, previous studies have shown that TAAT is effective in reducing body weight, WC, and body fat mass [14,29]; therefore, we did not consider a blank control group, instead, using an ILCD, according to its effect indicated in recent randomized trials [30,31].

TAAT appears minimal side effects, including the pain caused by local noninvasive stimulation that can be tolerated by most children [32]. As participants are recruited from the obesity clinic of the Department of TCM, randomization is set in a 3:1 ratio, allowing that needs of more participants are satisfied.

Maintaining compliance remains challenging to the young population. To ensure better compliance, we use methods such as regular reminders and random checks. To avoid bias, the outcome observer is unaware of the grouping of the participants.

In conclusion, we will evaluate the efficacy and safety of the TAAT in losing weight and improving the cardiometabolic risk of overweight or obese children with gastric-heat and dampness-obstruction syndrome. The results of this study will lead to an update of the consensus on TCM intervention for obesity. However, given the limitations of the intervention time in the experimental design, it is hoped that in future clinical trials, the intervention and follow-up time will be extended in order to obtain a long-term evaluation of the intervention effect.

### Conclusion

We conducted a pragmatic randomized controlled trial to investigate the effect and safety of TAAT compared with ILCD for overweight or obese children comorbid with at least one cardiometabolic risk factor. Furthermore, our study will investigate the participants’ differential responses of gut microbiota and serum biomarkers to examine underlying mechanisms. The protocol of our study will provide methodologic information and obtain interesting evidence from children for the 2 kinds of nonpharmacological interventions.

## Appendix

Multimedia Appendix 1 SPIRIT (Standard Protocol Items: Recommendations for Interventional Trials) checklist.

Multimedia Appendix 2 CONSORT (Consolidated Standards of Reporting Trials) checklist.

## Abbreviations

BP: blood pressure
GLM: generalized linear model
ILCD: intermittent low carbohydrate diet
SPIRIT: Standard Protocol Items: Recommendations for Interventional Trials
TAAT: TCM auricular acupressure treatment
TCM: traditional Chinese medicine
WC: waist circumference
